***3.0 BC-GP Method Overview***

***3.1 Verigene System Process***

DNA extraction is performed on the Processor SP via an automated pipettor that transfers reagents between reagent wells in the Extraction Tray and the Utility Tray with a single-use pipette tip. Gram-positive blood culture media is placed in the specimen well of the extraction tray by the operator. The remaining steps of the assay are performed by the Processor SP. The Processor SP lyses the bacterial cells and cleaves proteins to access the nucleic acids. The nucleic acids are then bound to magnetic microparticles (MMPs), also referred to as magnetic glass particles. The MMP-bound nucleic acids are washed to remove cellular debris and lysis buffer contaminants. The nucleic acids are eluted off the MMPs in the presence of elution buffer and increased temperature.

The Processor SP pipettor mixes a pre-determined volume of extracted DNA with appropriate panel-specific specimen buffer and transfers this solution to the Test Cartridge. All of the hybridization steps take place within the Test Cartridge. Microfluidic channels and pumps control the addition and removal of reagents from the hybridization chamber. The target detection process occurs with hybridization of the target analyte to a synthetic gene-specific oligonucleotide capture strand on the hybridization cartridge’s substrate. A synthetic mediator target specific oligonucleotide is included with the test-specific buffer to form a hybridization “sandwich” with the gene sequence of interest. Washing steps following the target hybridization remove the unbound DNA from the hybridization chamber. A probe, composed of a gold nanoparticle with covalently bound oligonucleotides complementary to a sequence on the intermediate oligonucleotide, is introduced after the target wash. After the probe hybridization is completed, a series of washing steps remove the unbound probe from the hybridization chamber. A two-part signal enhancement reagent is added to the hybridization chamber and reacts with the gold nanoparticle to amplify the signal for the Verigene Reader scanning and analysis. Once the test is completed, the Test Cartridge is removed from the Processor SP unit and the Reagent Pack is removed and discarded. The Substrate is then imaged and analyzed on the Reader.

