***4.0 Experimental Design***

The Study will evaluate the performance of the BC-GP test in comparison to a comparator reference method performed at a central clinical microbiology service laboratory (traditional culture/biochemical identification/susceptibility as relevant for each panel member). Cefoxitin will be used as a surrogate for detecting methicillin/oxacillin resistance. Bi-directional sequencing, performed by a third-party sequencing vendor, will be used to identify *vanA* and *vanB*.

The study will be conducted at 5 clinical centers. Each site will be provided with operation manuals, standard operating protocols, and “hands-on” training to ensure competency in executing the BC-GP test.

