***5.2 Process for Testing Fresh Specimens (Refer to flow chart on Page 15):***

Each study site will de-identify the fresh propectively-collected specimen and assign a Nanosphere specimen ID number. Pre-printed labels will contain this de-identified Nanosphere specimen ID number and additional identifiers for labeling Tubes A-D as described below. Each site will be responsible for specimen blinding and de-identification of the fresh specimens that they are testing.

Gram Positive blood culture media will be aliquoted into Tubes A and B. Tube A (1.5mL of blood culture media) will be designated for Verigene Testing and Tube B (1mL of blood culture media) will be immediately stored frozen at ≤ -70°C.

To ensure homogeneity in the aliquots, the following process should be followed for each bottle type:

1). BACTEC™ Plus Aerobic/F (92) Bottles (or similar):

Invert the bottle several times to mix the media and insert the needle into the bottle using aseptic practices. Place the beveled edge of the needle against the sidewall of the bottles to prevent resin from being aspirated.

2). For BacT/ALERT® FA FAN® Aerobic bottle (or similar):

Invert the bottle several times to mix the media and insert the needle into the bottle using aseptic practices. The media will likely contain charcoal which is acceptable as long as the media is homogenous.

Each Verigene test requires 350uL of blood culture media and will take place within 12 hours of initial blood culture bottle positivity (as measured by the blood culture monitoring instrument).

Tube A will be stored at room temperature during Verigene testing. Tube A will be stored frozen at

≤ -70°C after repeat testing is completed (if needed). Repeat tests on the Verigene due to pre-analysis errors or no calls will be done using blood culture media from Tube A within 24 hours of initial blood culture bottle positivity. If the repeat test cannot be repeated within 24 hours, freeze Tube A at ≤ -70°C until testing can be done and follow the thawing directions in the frozen specimen processing section below.

Residual DNA from each Methods Comparison specimen test will be collected from the Verigene Extraction Tray and stored in Tube C at ≤ -70°C.

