In addition, during the aliquoting process, a TSA with 5% Sheep Blood Agar Plate (BBL 221261 or equivalent) will be inoculated from the Gram-positive blood culture bottle. Following incubation at 34-36°C (35°C preferred) for 24 hours, two glycerol stocks will be made from each unique colony type on the plate. The plate will be reincubated for an additional 24 hours and observed for additional unique colony types. If additional unique colony types are observed then two glycerol stocks will be made. The glycerol stocks will be frozen at ≤ -70°C. One set of glycerol stocks will be retained at the study site and the second set of glycerol stocks will be shipped to a third-party service lab for confirmatory identification and methicillin/vancomycin susceptibility (if applicable) by traditional biochemical methods.

The third-party service lab will be responsible for plating the glycerol stocks, making a secondary set of glycerol stocks, and performing traditional biochemical analysis for confirmatory identification. Each unique colony type will also be tested on an automated identification card (e.g., VITEK, Phoenix or similar) to genus and species level by the third-party service laboratory. A methicillin AST or cefoxitin disk test (depending on common practices at the study site) will be performed on Staphylococcus aureus and Staphylococcus epidermidis isolates to determine methicillin resistance. A vancomycin AST or e-test (depending on common practices at the study site) will be performed on Entercoccus faecalis and Enterococcus faecium isolates to determine vancomycin resistance. The residual DNA from Tube C will be tested by bi-directional sequencing at a third-party sequencing laboratory for these vancomycin-resistant isolates to determine if vanA or vanB are present.

The table below provides a list of each tube (A-D), its designated contents, and use.

| Tube A | 1.5mL | Verigene Testing (350uL per test) |
| --- | --- | --- |
| Tube B | 1mL | Downstream Discrepancy Analysis (if required) |
| Tube C | - | Residual DNA from Verigene Extraction Tray |
| Tube D  Set 1 | - | Glycerol Stock retained at site. |
| Tube D  Set 2 | - | Glycerol Stock shipped to third-party service lab. |

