***5.4 Repeat Testing***

**5.4.1** If an error occurs during test processing that prevents a BC-GP Test substrate from being analyzed in the Verigene Reader, it is classified as a pre-analysis error. The recommended recourse for a pre-analysis error is one-time repeat testing of the specimen. Pre-analysis errors are to be excluded from call rate calculations but included in a pre-analysis error rate calculation.

**5.4.2** If a test results in a “no call”, the test should be repeated once as per the package insert and this result will be considered to be the final result for that specimen.

**5.4.3** If no residual DNA is present in the extraction tray after testing, the test should be repeated once.

**5.4.4** If a test results in a “no call-no grid”, verify the silver tape is removed from the slide and check that the orientation of the slide is flush with the holder. The slide may be re-scanned. If it cannot be rescanned the test should be repeated once.

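### The sequencing that assigns vanA or vanB uses the BC-GP run's own leftover extract, so the gene reference is not independent of the test's extraction; 5.4.3 also leaves the analysed result undefined after a repeat

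*Protocol*

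**What the plan says.** Section 4.0 of the Protocol makes sequencing the means of gene assignment: "Bi-directional sequencing, performed by a third-party sequencing vendor, will be used to identify" vanA and vanB. Sections 5.2 (fresh) and 5.3 (frozen) name the material: "The residual DNA from Tube C will be tested by bi-directional sequencing at a third-party sequencing laboratory for these vancomycin-resistant isolates". Both sections also give its origin: "Residual DNA from each Methods Comparison specimen test will be collected from the Verigene Extraction Tray and stored in Tube C".

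Section 3.1 shows that this extract is what the test itself reads: "The Processor SP pipettor mixes a pre-determined volume of extracted DNA with appropriate panel-specific specimen buffer and transfers this solution to the Test Cartridge".

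Before sequencing there is a separate phenotypic step: "A vancomycin AST or e-test (depending on common practices at the study site) will be performed on Entercoccus faecalis and Enterococcus faecium isolates". Only specimens found resistant go on to sequencing. Isolate material is also kept: "two glycerol stocks will be made from each unique colony type on the plate", and one set (Tube D Set 2) goes to the third-party service laboratory, which plates it.

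On repeats, section 5.4.3 says: "If no residual DNA is present in the extraction tray after testing, the test should be repeated once". Section 5.4.2 names the final result after a no call; section 5.4.3 names none.

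**The concern.** A reference standard should be able to contradict the test. Here the gene reference starts from DNA that the test has already extracted. If that extraction recovers too little of the van target, both the cartridge and the sequencer may miss the gene. If the extract is contaminated with van DNA, both may report it. Either way the two agree and are wrong together, and a discordant work-up that starts from disagreement between them would not begin.

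At stake is the criterion in section 6.1: 95% sensitivity for each analyte, with the lower bound of the two-sided 95% confidence interval above 90%. If a resistant specimen whose Tube C sequences negative is counted as van-negative, a test miss leaves the denominator and apparent sensitivity rises. The sections shown do not say how such a specimen is classified.

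The second issue is narrower. A valid BC-GP call can be followed by a second result only because the tray held no leftover DNA, and nothing says which of the two is analysed. The wording covers every specimen, so it reaches all analytes and not only the resistance genes.

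**Working it through.** **No plan figure to reproduce.** The Protocol gives 100 to 300 specimens at each of 5 sites (500 to 1,500 in all) but no expected count of vanA or vanB carriers, no miss rate and no rate of shared failure. The arithmetic below illustrates how the mechanism works; it does not estimate its size.

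**Step 1: where test and reference share material.**

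| Step | Material | Independent of the BC-GP extract? |
|---|---|---|
| BC-GP van call (3.1) | Portion of the Processor SP extract | It is the test |
| Vancomycin AST or e-test (5.2, 5.3) | Cultured isolate | Yes |
| Sequencing for vanA/vanB (5.2, 5.3) | Tube C, remainder of the same extract | No |
| Isolate stock, Tube D Set 2 (5.2, 5.3) | Regrown colony | Yes, but not the material named for sequencing |

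The resistance phenotype is independent of the extract; the gene label is not.

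**Step 2: what a shared miss does to sensitivity.** Assumptions: 100 resistant specimens truly carrying the gene, 8 missed by BC-GP, and *k* of those 8 also sequencing negative from Tube C and then counted as reference-negative. Then

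apparent sensitivity = 92 / (100 − k),

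with the exact (Clopper-Pearson) two-sided 95% lower bound, which is the 2.5% quantile of Beta(92, 9 − k).

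| Shared misses k | Ratio | Sensitivity | Lower bound | Criterion |
|---|---|---|---|---|
| 0 | 92/100 | 92.0% | 84.8% | fail |
| 2 | 92/98 | 93.9% | 87.1% | fail |
| 4 | 92/96 | 95.8% | 89.7% | fail |
| 5 | 92/95 | 96.8% | 91.05% | pass |
| 8 | 92/92 | 100% | 96.1% | pass |

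The result changes only from k = 5 upward. At k = 0 there is no bias.

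**Step 3: a second view.** Assume 97% detection once target DNA has been extracted, 100 carriers, and every target-extraction failure shared with sequencing.

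| Extraction failure | Independent reference | Tube C reference |
|---|---|---|
| 0% | 97/100, lower bound 91.5% | 97/100, lower bound 91.5% |
| 2% | 95/100, lower bound 88.7% | 95/98, lower bound 91.3% |
| 5% | 92/100, lower bound 84.8% | 92/95, lower bound 91.0% |
| 10% | 87/100, lower bound 78.8% | 87/90, lower bound 90.6% |

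If about half of the failures are shared in the 5% case, the result is 92/98 with a lower bound of 87.1%, still a fail.

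**Step 4: the repeat rule.** Sections 5.2 and 5.3 name pre-analysis errors and no calls as reasons to repeat from Tube A. Section 5.4.3 adds absence of residual DNA, without asking whether the call was valid. Only 5.4.2 says which result is final, and it covers no calls only.

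**The case against.** The strongest case on the other side has five parts.

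- **The phenotype is a real safeguard.** AST or e-test on the isolate does not depend on the extract. A gene lost from the extract would show up as a resistant enterococcus with negative sequencing, which is visible. Section 6.1 includes susceptibility in the reference method, so a van-negative BC-GP call in that specimen could be read as discordant and sent to section 6.2. This stands, and it confines the problem to gene assignment in resistant specimens. It does not close the gap, because section 4.0 gives sequencing the gene assignment and the text shown has no rule for the resistant, sequence-negative specimen. Attachment F, which lists reference methods by analyte, is not available here.
- **Shared contamination is limited.** Susceptible isolates are not sequenced, so a false van-positive call there is not confirmed by the shared extract. This stands.
- **The process control screens extraction.** Under section 4.4.1, PC1 must be detected or the result is a no call. This catches gross failure. PC1 is *Bacillus subtilis*, so its detection does not prove adequate recovery of an enterococcal van target.
- **Mixed cultures.** A reader might infer that whole-specimen DNA is invalid because it cannot be tied to the resistant isolate. Section 1.2 describes the van claim for positive specimens, and the test cannot tie the gene to an isolate either. This is not a separate fault.
- **Direction of the repeat bias.** A reader might infer that 5.4.3 selectively gives false negatives a second chance. Nothing in the Protocol links absence of leftover DNA to low target yield or to missed calls, and a repeat could equally turn a correct call into a miss. That the rule exists to fill Tube C is also an inference. Only the missing statement of which result counts is established.

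**Conclusion.** The gene reference for vanA and vanB is not independent of the index test's extraction; this follows from the text without inference. The exposure covers only vanA, vanB or neither in phenotypically resistant E. faecalis and E. faecium, and arises from target-specific extraction loss or contamination that PC1 does not detect. Sensitivity is inflated only if resistant, sequence-negative specimens are counted as van-negative, which the text shown neither states nor excludes.

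A reader might conclude that the van sensitivity result is bound to be biased upward, or that a failing test would pass. The documents do not support that. The rate of shared failure is unknown, hybridization and reading steps after extraction also cause misses that are not shared, and in the assumed case of 100 carriers and 8 misses at least 5 of the 8 must be shared to change the outcome.

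Section 5.4.3 leaves the analysed result undefined after a repeat of a valid test; the direction of any bias from this is not known.

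This is a cheap improvement that should be made, held with moderate confidence.

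**What to change.** 1. In sections 5.2 and 5.3, sequence DNA prepared from the vancomycin-resistant isolate regrown from Tube D Set 2. Keep Tube C as exploratory or back-up material.
2. State that a resistant specimen with negative sequencing is handled as discordant under section 6.2 and is not reference-negative by default.
3. In section 5.4.3, state that a valid first BC-GP call is the analysed result and that a repeat under this rule supplies DNA only.

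The cost is one DNA preparation per vancomycin-resistant isolate, a slightly longer turnaround for the van results, and a few sentences of protocol text. The third-party laboratory already plates these stocks, so no new specimen is needed.

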***1.2 Test Overview***

The Verigene Gram-Positive Blood Culture (BC-GP) Nucleic Acid Test is a multiplexed assay that is designed to simultaneously detect and identify bloodstream infection (BSI) -causing, gram-positive bacteria. The test is performed on the Verigene System as a qualitative in vitro diagnostic test used for the identification of potentially pathogenic, gram-positive bacteria and is an aid to the identification of gram-positive bacteria bloodstream infections. It is not, however, used to monitor bloodstream infections.

The BC-GP test is performed directly on positive blood culture media specimens, using aerobic blood culture bottles, which are determined to have gram-positive bacterial growth by Gram stain.

The BC-GP test detects and identifies the following bacterial genera and species:

*·         Staphylococcus spp.*

*·         Streptococcus spp.*

*·         Micrococcus spp.*

*·         Listeria spp.*

*·         Staphylococcus aureus*

*·         Staphylococcus epidermidis*

*·         Staphylococcus lugdunensis*

*·         Streptococcus pneumonia*

*·         Streptococcus pyogenes*

*·         Streptococcus agalactiae*

*·         Streptococcus anginosus Group*

*·         Enterococcus faecalis*

*·         Enterococcus faecium*

In addition, the BC-GP test detects the *mecA* resistance marker, if present, in *Staphylococcus aureus*-positive specimens and *Staphylococcus epidermidis*-positive specimens.  The BC-GP test also detects the *vanA* or *vanB* resistance markers, if present, in *Enterococcus faecalis*-positive specimens and *Enterococcus faecium*-positive specimens.

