***4.1 Equipment and Materials***

***4.1.1 Provided by Nanosphere***

- Verigene Instruments:
  - Verigene Reader (Nanosphere Item #10-0000-02)
  - Verigene Processors SP (Nanosphere Item #10-0000-07 or #10-0000-08)
- Postscript 2 compatible printer; parallel or Ethernet network connection
- Training Specimens
- Nuclease-free 2.0 mL cryovials and 0.6 mL microcentrifuge tubes
- BBL Prepared Tubed Media for Long-Term Maintenance of Microorganisms Trypticase Soy Broth with 20% Glycerol (BD#297808)
- Specimen, plate, and tube identification labels
- Sequencing services at a third site as needed (in particular to differentiate *vanA* and *vanB* isolates if vancomycin resistance is present)
- Culture identification services at a third site as needed
- Verigene BC-GP test supplies:
  - BC-GP (BSI+) Extraction Trays/Tip Holder Assemblies
  - BC-GP (BSI+) Test Cartridges
  - BC-GP (BSI+) Utility Trays
  - BC-GP (BSI+) Processing Control 1 Tubes

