Each unique colony type will also be tested on an automated identification card (e.g. VITEK, Phoenix or similar) to genus and species level by the third-part service laboratory. A methicillin AST or cefoxitin disk test (depending on common practices at the study site) will be performed on Staphylococcus aureus and Staphylococcus epidermidis isolates to determine methicillin resistance. A vancomycin AST or e-test (depending on common practices at the study site) will be performed on Entercoccus faecalis and Enterococcus faecium isolates to determine vancomycin resistance. The residual DNA from Tube C will be tested by bi-directional sequencing at a third-party sequencing laboratory for these vancomycin-resistant isolates to determine if vanA or vanB are present.

The third-party service lab will be responsible for plating the glycerol stocks, making a secondary set of glycerol stocks, and performing traditional biochemical analysis for confirmatory identification.

The table below provides a list of each tube (A-D) and its designated contents and use.

| Tube A | 1.5mL | Verigene Testing (350uL per test) |
| --- | --- | --- |
| Tube C | - | Residual DNA from Verigene Extraction Tray |
| Tube D  Set 1 | - | Glycerol Stock retained at site. |
| Tube D  Set 2 | - | Glycerol Stock shipped to third-party service lab. |

All blood culture media specimens and DNA samples will be shipped to the sponsor on a pre-determined schedule under appropriate shipping conditions. All glycerol stocks will be shipped to the third-party service lab (or alternate site if necessary) on a pre-determined schedule under appropriate shipping condition.

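### vanA/vanB sequencing is limited to phenotypically vancomycin-resistant isolates, so the gene reference is only partly verified and sensitivity may be overstated

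*Protocol*

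**What the plan says.** Protocol section 1.2 describes what the test claims: it detects the vanA or vanB "resistance markers, if present, in" specimens positive for E. faecalis or E. faecium. That statement carries no condition on phenotype.

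Section 4.0 gives the method for these markers, also without a phenotype condition: "Bi-directional sequencing, performed by a third-party sequencing vendor, will be used to identify" vanA and vanB.

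Section 5.2 (fresh specimens) puts a phenotypic step first: "A vancomycin AST or e-test (depending on common practices at the study site) will be performed on Entercoccus faecalis and Enterococcus faecium isolates". Tube C DNA is then sequenced "for these vancomycin-resistant isolates to determine if vanA or vanB are present". Section 5.3 (frozen specimens) has the same restriction: "The residual DNA from Tube C will be tested by bi-directional sequencing at a third-party sequencing laboratory for these vancomycin-resistant isolates". The materials list in 4.1.1 agrees, offering sequencing "in particular to differentiate *vanA* and *vanB* isolates if vancomycin resistance is present".

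Section 6.1 asks for sensitivity and specificity for each analyte with two-sided 95% intervals. The acceptance criterion is 95% with a lower bound above 90%. The same section describes the reference method as culture with biochemical identification and susceptibility. Section 6.2 makes sequencing of discordant results optional.

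**The concern.** The test makes a claim about genotype, but the genotypic reference is applied only after a positive phenotype. A specimen whose Enterococcus isolate is not called resistant has no route to a gene-positive reference status, whatever it carries. The protocol also does not mention intermediate results, so whether they trigger sequencing is undefined.

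Suppose the unsequenced isolates are scored gene-negative, which is the natural way to obtain a specificity. Carriers without phenotypic resistance then fall into two groups:

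- **Detected by BC-GP.** They appear as false positives and lower the reported specificity, unless someone chooses to sequence them under 6.2.
- **Missed by BC-GP.** They agree with the reference, look like true negatives and never enter discordant resolution. They drop out of the sensitivity denominator.

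The second group matters more. No later analysis can recover sequences that were not obtained, and the acceptance rule leaves little room for misses in a marker with few carriers.

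**Working it through.** **Inputs from the protocol.** The criterion is a lower two-sided 95% bound above 90% (6.1). There are 100-300 specimens at each of 5 sites (5.1), so 500-1500 in total. The protocol states no number of van carriers and no rate of discordance between gene and phenotype, so there is no figure to reproduce. All counts below are assumptions.

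**Step 1: what the gate does to the estimates.** Let R be carriers with phenotypic resistance, S carriers without it, and N0 true non-carriers. Let Se_R and Se_S be the detection rates in the two carrier groups, and Sp the true specificity. If S is scored negative:

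- Apparent sensitivity = Se_R
- True sensitivity = (R·Se_R + S·Se_S)/(R + S)
- Apparent specificity = [N0·Sp + S·(1 − Se_S)]/(N0 + S)

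If S = 0, both apparent values equal the true ones. If Se_S = Se_R, sensitivity is unbiased in expectation. It is inflated only when Se_S < Se_R.

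**Step 2: range under assumptions.** Take 60 carriers, Se_R = 97% and Sp = 99%. Apparent sensitivity is 97.0% in every row.

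| Carriers not resistant | Se_S | True Se | Apparent Sp, N0 = 90 | Apparent Sp, N0 = 1000 |
|---|---|---|---|---|
| 0% | any | 97.0% | 99.0% | 99.0% |
| 5% | 97% | 97.0% | 95.9% | 98.7% |
| 5% | 70% | 95.7% | 96.8% | 98.8% |
| 10% | 97% | 97.0% | 93.0% | 98.4% |
| 10% | 70% | 94.3% | 94.7% | 98.6% |
| 20% | 97% | 97.0% | 87.7% | 97.9% |
| 20% | 70% | 91.6% | 90.9% | 98.2% |

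Example for 20% and Se_S = 70%: R = 48 and S = 12. True Se = (48 × 0.97 + 12 × 0.70)/60 = 54.96/60 = 91.6%. Apparent Sp with N0 = 90 is (89.1 + 3.6)/102 = 90.9%.

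**Step 3: how few specimens decide the criterion.** The Clopper-Pearson lower bound is 0.025^(1/n) when all n are detected, and otherwise the 2.5% quantile of Beta(x, n − x + 1). The smallest n with a bound above 90% is 36 with no misses, 54 with one and 70 with two (Wilson: 35, 53 and 69).

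- Reported 40/40: 0.025^(1/40) = 91.2%, pass.
- True 40/41 = 97.6%, with one hidden missed carrier: lower bound 87.1%, fail.

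From these minima, with every resistant carrier detected, a single hidden miss reverses the result for any count of resistant carriers from 36 (first pass with none missed) to 52 (53 in all with one missed, one short of 54).

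**Step 4: specificity depends on the denominator.** Assume 3 non-resistant carriers, all detected by BC-GP and none sequenced.

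- Denominator of 80 non-resistant enterococci: 77/80 = 96.3%, lower bound 89.4%, fail. With 2 instead of 3, 78/80 has lower bound 91.3%, pass.
- All specimens less 40 positives: 457/460 = 99.3% (lower bound 98.1%) to 1457/1460 = 99.8% (lower bound 99.4%), both pass easily.

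**Step 5: does section 6.2 repair it?** Its first step compares with the automated phenotypic system, which 5.2 and 6.1 describe as identification to genus and species, so it cannot settle a gene question. Sequencing there is optional and reaches only discordant specimens. If detected carriers are rescued and missed ones are not, reported sensitivity is (R·Se_R + S·Se_S)/(R + S·Se_S). In the 20%, Se_S = 70% case this is 54.96/56.4 = 97.4%, against a true 91.6%. The rescue can remove the specificity bias but leaves the sensitivity bias in place.

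**The case against.** The strongest defence is that the protocol describes a coherent two-step comparator: susceptibility testing establishes resistance, and sequencing then tells vanA from vanB. Section 4.1.1 says this outright, and 6.1 includes susceptibility in the reference method. For a resistance marker that is a legitimate choice. It would, however, support a claim of agreement with phenotype plus gene typing of resistant isolates. It does not verify a claim that the gene is detected whenever present.

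A reader might infer that unsequenced isolates are recorded as gene-negative and that both accuracy measures are therefore wrong. The protocol supports neither statement:

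- It does not say how unsequenced isolates are classified or which specimens form the specificity denominator. That may properly be left to the statistical analysis plan, which is not at hand.
- Bias needs carriers without phenotypic resistance, and no rate is given. Nor does the protocol give any basis for treating one of the two genes as more exposed than the other.
- Sensitivity is inflated only if such carriers are detected less often than resistant ones.
- The two harms pull on the same specimens. A given carrier is either detected or missed, so both cannot occur at full size.
- Detected carriers would surface as discordant and could be sequenced under 6.2.
- The specificity failure needs a small, enterococci-only denominator and at least three such specimens among 80.

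All of this stands and limits the point. It does not reach the carrier that is neither resistant nor detected: the sequencing trigger is a laboratory rule set in the protocol, and no analysis plan can supply the missing reference result.

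**Conclusion.** The point holds in conditional form. Sequencing for vanA/vanB is restricted to phenotypically resistant isolates, while the test's claim and the method named in 4.0 concern the gene itself. This is partial verification.

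If unsequenced isolates are taken as gene-negative, sensitivity may be overstated, and specificity may be understated where 6.2 sequencing is not used. The size cannot be fixed from the protocol: it is zero if no non-resistant carriers occur. In the assumed range of Step 2, true sensitivity runs from 97.0% down to 91.6% behind a reported 97.0%. At 40 detected resistant carriers, one hidden miss is enough to change pass to fail. The specificity effect is of practical weight only with a denominator limited to enterococci.

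This is a worthwhile improvement at low cost. It is not evidence that the study's van results will be wrong.

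**What to change.** In sections 5.2 and 5.3, sequence the stored Tube C DNA of every E. faecalis or E. faecium specimen for vanA and vanB, regardless of the susceptibility result and without sight of the BC-GP result.

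If that is too much, sequence at least all isolates that are not susceptible, naming intermediate results explicitly, plus a random sample of susceptible ones. Analyse with a correction for verification bias. The sample must be large enough to be informative: finding no carriers among 30 would still allow a carriage rate up to 1 − 0.025^(1/30) = 11.6% (upper two-sided 95% limit).

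If some isolates remain unsequenced, state in 6.1 that their van comparison is against phenotype, and limit the vanA/vanB accuracy claim accordingly.

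The cost is modest: residual DNA from each specimen test is already kept in Tube C and a third-party sequencing vendor is already part of the design. The change therefore needs an amendment and additional sequencing reactions, with no new collection.
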